### Safety reporting

#### Adverse events (AEs), serious adverse events (SAEs) and SUSARs

##### Adverse events

AEs are defined as any undesirable experience occurring to a subject during the study, whether or not considered related to the investigational product. Since patients admitted to an ICU are critically ill and present with many AEs, only possible adverse drug-related events (on days of study drug administration: prolonged QTc by EKG, muscle rigidity and associated movements disorders (Simpson Angus Scale)), as indicated by the subject or observed by the investigator or his staff occurring from the date of randomisation until 14 days later or discharge from ICU or death (whichever comes first), will be recorded in the CRF. In addition, the following AEs will be assessed daily during 14 days after randomisation: epilepsy, tachycardia, hypotension (not explained otherwise), hepatic dysfunction (not explained otherwise), leucopenia (not explained otherwise) and bronchospasms (not explained otherwise).

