**Methods and analysis:**

EuRIDICE is a prospective, multi-centre, randomised, double-blind, placebo-controlled trial. Study population consists of adult intensive care unit (ICU) patients without acute neurological injury who have delirium based on a positive Intensive Care Delirium Screening Checklist (ICDSC) or Confusion Assessment Method for the ICU (CAM-ICU) assessment. Intervention is intravenous haloperidol 2.5 mg (or matching placebo) every 8 hours, titrated daily based on ICDSC or CAM-ICU positivity to a maximum of 5 mg every 8 hours, until delirium resolution or ICU discharge. Main study endpoint is delirium and coma-free days (DCFD) up to 14 days after randomisation. Secondary endpoints include (1) 28-day and 1-year mortality, (2) cognitive and functional performance at 3 and 12 months, (3) patient and family delirium and ICU experience, (4) psychological sequelae during and after ICU stay, (4) safety concerns associated with haloperidol use and (5) cost-effectiveness. Differences in DCFDs between haloperidol and placebo group will be analysed using Poisson regression analysis. Study recruitment started in February 2018 and continues.

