#### Exclusion criteria for randomisation

Prolonged QT-interval (QTc >500 ms).(recent) TdP.(recent) Neuroleptic malignant syndrome or parkinsonism.Evidence of acute alcohol (or substance) withdrawal requiring pharmacological intervention (eg, benzodiazepines or alpha-2 agonist) to treat.The patient is expected to die within 24 hours or expected to leave the ICU within 24 hours.No (previously) signed informed consent by patient or representative.Current participation in another intervention trial that is evaluating a medication, device or behavioural intervention.

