#### Dosages, dosage modifications and method of administration

The following dosing scheme will be used: start with haloperidol/placebo (further called: ‘study drug’) 2.5 mg intravenously q8h (because of delirium screening once every 8-hour shift) and increase to a maximum dose of 5 mg intravenously q8h when delirium persists during the next 8-hour shift. Doses will be reduced (50% of dose) in the very old elderly (age ≥80 years). The study drug dose will be decreased (when dosage is 5 mg intravenously q8h) or stopped (when dose is 2.5 mg intravenously q8h) when delirium has resolved (or is un-assessable due to coma) for the next 24 hours (implying: three consecutive delirium assessments during three shifts). Dosages can be lowered also at the discretion of the treating physician in case of evident rigidity, which is in line with current routine practice. Standard clinical practice for the administration of haloperidol will be followed.

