##### Serious adverse events

An SAE is any untoward medical occurrence or effect, occurring during the 14-day study period at the ICU, that (the SAEs for the purpose of the study are shown in *italics* per item)

Results in death;Death will always be reported as an SAEIs life threatening (at the time of the event);
*Ventricular arrhythmia or malignant neuroleptic syndrome*
Requires hospitalisation or prolongation of existing inpatients’ hospitalisation;
*Not to be expected; only applicable when the site investigator is able to explicitly show a relationship*
Results in persistent or significant disability or incapacity;
*Not to be expected; only applicable when the site investigator is able to explicitly show a relationship*
Is a congenital anomaly or birth defect; (*Not applicable*) orAny other important medical event that did not result in any of the outcomes listed above due to medical or surgical intervention but could have been based on appropriate judgement by the investigator.

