### Statistical analysis

### Primary and secondary study parameter(s)

Statistical analysis will be done according to intention-to-treat principle. All randomised participants will be included. The primary outcome is DCFDs, defined as the number of days in the first 14 days after randomisation during which the patient is alive without delirium and not in coma from any cause.^7^ Patients who are discharged before the 14-day study period has ended will be recorded as delirium and coma free after discharge.^8 35^ In addition, we will assume all patients who died within 14 days after randomisation to have 0 DCFDs.^7^ Differences between DCFDs between the haloperidol group and placebo group will be analysed using Poisson regression analysis, with adjustment for differences in baseline characteristics between treatment groups (when present) and for the different centres. We will collect data with regards to baseline demographics: age, sex, admission diagnosis category, APACHE II and APACHE IV, Sequential Organ Failure Assessment (SOFA) score, ICU days before study entry and pre-admission delirium duration in participants with delirium on admission. Pre-defined sub-analyses will include efficacy stratified by (1) agitated, mixed-type or hypoactive delirium; (2) the presence of hallucinations or delusions; (3) delirium severity (based on ICDSC score: low delirium severity=mean ICDSC score of 4 to 5; medium delirium severity=mean ICDSC score 5 to 7; high delirium severity=ICDSC score 7 to 8); and (4) sedation-related, hypoxic, metabolic or septic delirium. For cognitive and functional outcomes assessed with designated test batteries, non-parametric or parametric tests will be used depending on normality of scaled test results. Mortality risk will be assessed as a binary endpoint. A more detailed statistical analysis plan, to be drawn up before Data Base Lock, will be drafted for publication separately.

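### The stated stop rule for study drug has no day limit, while adverse event recording and the SAE definition close at day 14, so any later dosing falls outside them

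*Protocol article*

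**What the plan says.** **End of dosing.** The abstract (Methods and analysis) gives study drug "until delirium resolution or ICU discharge". The section on dosages and dosage modifications gives the working rule. The dose is lowered (from 5 mg every 8 hours) or stopped (from 2.5 mg every 8 hours) "when delirium has resolved (or is un-assessable due to coma) for the next 24 hours", which it explains as "three consecutive delirium assessments during three shifts". The randomisation section replaces a used box with another from the same kit and puts no limit on boxes or days.

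**End of safety recording.** The Adverse events section enters drug-related events (QTc prolongation, rigidity and movement disorders on days of drug administration) in the case record form if "occurring from the date of randomisation until 14 days later or discharge from ICU or death (whichever comes first". It then says that "the following AEs will be assessed daily during 14 days after randomisation", and names six: epilepsy, tachycardia, hypotension, hepatic dysfunction, leucopenia and bronchospasm. The Serious adverse events section defines an SAE as an event "occurring during the 14-day study period at the ICU", and gives ventricular arrhythmia and malignant neuroleptic syndrome as the life-threatening ones.

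**Other uses of the 14 days.** The statistical section uses the same period to score the primary outcome: patients "discharged before the 14-day study period has ended will be recorded as delirium and coma free". Nowhere is it written as a limit on dosing.

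**The concern.** Recording of harms should last at least as long as exposure to the drug. The plan appears to accept this, because it ties the recording of QTc and rigidity to days on study drug, but the day-14 limit then breaks the link for anyone dosed longer.

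Haloperidol's safety is part of the trial's stated aim. Malignant neuroleptic syndrome is serious enough to bar entry (the randomisation exclusions list recent "Neuroleptic malignant syndrome or parkinsonism"), yet the only place that names it as an event to collect is the SAE list. The stopping rules under Premature termination are also framed in terms of serious adverse reactions or events, so a late event that does not meet the SAE definition has no stated route into them.

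**Working it through.** The plan gives no figure for dosing after day 14, so the check compares two stated rules and works out when they diverge.

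**1. Maximum dose.** 5 mg × 3 doses = 15 mg/day, which agrees with the daily maximum in the dosage justification. Half of that from age 80 is 7.5 mg/day.

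**2. The two rules side by side.**

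| | Ends at | Day limit |
|---|---|---|
| Study drug | delirium resolved, or un-assessable through coma, over 24 h; or ICU discharge | none stated |
| Drug-related AEs in the case record form | first of day 14, ICU discharge, death | day 14 |
| Six other listed AEs | day 14 | day 14 |
| SAE definition | end of the 14-day period in the ICU | day 14 |

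Discharge and death close both sides together. The mismatch is confined to patients who are alive, in the ICU and not yet stepped off the drug at day 14.

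**3. When they diverge.** The recording window is 14 × 24 = 336 h. Stopping from 2.5 mg every 8 hours needs three 8-hour shifts, 3 × 8 = 24 h. A positive screen later than about 336 − 24 = 312 h (the fourteenth day) therefore carries dosing past the window if the patient stays in the ICU and the drug is not held for another reason. From 5 mg every 8 hours the dose is first lowered. If the second step needs its own 24 h, which the text does not say outright, the lag is 48 h and the point moves to 336 − 48 = 288 h (the thirteenth day). These cut-offs are approximate, since the window is counted from the date of randomisation. Coma for 24 h, a hold for persistent QTc prolongation, or a dose reduction for rigidity can lower or interrupt dosing.

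**4. What is lost and what is kept after day 14.**

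- *Lost:* malignant neuroleptic syndrome as a named event; the six listed AEs; the SAE status of ventricular arrhythmia.
- *Kept:* daily QTc measurement (Patient assessments) and EKG and Simpson Angus checks while on drug (Table 1); QTc, rigidity and ventricular arrhythmia as outcomes during ICU stay (Secondary study outcomes); deaths in the 28-day and 12-month mortality outcomes. Deaths are arguably also kept as SAEs, because the SAE section says they are always reported as such.

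**5. How many patients.** This cannot be derived from the document. If time on drug were exponential with mean m days, the share still on drug at day 14 would be exp(−14/m). Assumed means of 3, 5, 7 and 10 days give about 1%, 6%, 14% and 25%, or roughly 7, 45, 100 and 183 of 742. The means are assumptions, and the spread shows only that the count depends on something the plan does not report.

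**The case against.** The strongest reply is that this is a condensed article and that maximum treatment duration belongs in the full protocol. The wording also hints at a 14-day frame. The SAE section speaks of a 14-day study period in the ICU, and Table 1 places the delirium screens that drive dosing, and the on-drug checks, in an ICU study period. If these are the same period, dosing ends at day 14 and no gap exists.

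Part of this stands. A cap may well have been intended, and the full protocol may state one. But the equation of the two periods is an inference, and the article does more than stay silent. It states when drug stops, in two places, and when recording stops, and the two do not agree.

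Three stronger readings are tempting, and the document supports none of them:

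- *Patients dosed after day 14 are unmonitored.* They are not. QTc and rigidity checks continue on drug, and ventricular arrhythmia and mortality are outcomes in their own right.
- *Every patient with a positive screen after hour 288 is dosed past day 14.* That needs the assumed second 24-hour step, and it ignores the coma branch and QTc holds.
- *The low planning means (3.2 and 4.2 delirium- and coma-free days) show that many patients are dosed late.* They do not. Coma days count against the endpoint but stop the drug, deaths score zero, and the affected days may fall early.

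**Conclusion.** The point holds as a mismatch between two stated rules. If the rules are followed as written, a patient still delirious in the ICU near or after day 14 receives study drug outside AE recording and outside the SAE definition. For that patient the unrecorded exposure is at most 15 mg/day (7.5 mg/day from age 80) on each later day of dosing, in the haloperidol arm.

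The consequence is limited to formal safety capture. The primary endpoint is unaffected, and much of the monitoring continues. How many patients are involved is unknown; it is zero if dosing was meant to end at day 14. The conclusion rests on reading the abstract and the dosing section as the complete stop rule, since no other part of the article caps dosing. It is worth correcting because the loss falls on serious, drug-specific events and the correction is small.

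**What to change.** Either of two changes closes the gap.

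1. **If a cap was intended:** add to the abstract and the dosing section that study drug stops at day 14 at the latest. This adds no data collection.
2. **If dosing may continue:** leave the present AE and SAE windows as they are and, only for patients still on study drug in the ICU after day 14, extend AE and SAE recording to 24 hours after the last dose. The cost is a few more days on existing forms for those patients.

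The second change should stay confined to that group. Running every patient's window to the later of day 14 or 24 hours after the last dose would remove the ICU-discharge limit, and would oblige sites to collect events on the ward to day 14 for everyone who leaves the ICU early. Under the second change, observation time in the extended group depends on how long delirium lasts, so events after day 14 are best reported separately from the fixed 14-day comparison.

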##### Serious adverse events

An SAE is any untoward medical occurrence or effect, occurring during the 14-day study period at the ICU, that (the SAEs for the purpose of the study are shown in *italics* per item)

Results in death;Death will always be reported as an SAEIs life threatening (at the time of the event);
*Ventricular arrhythmia or malignant neuroleptic syndrome*
Requires hospitalisation or prolongation of existing inpatients’ hospitalisation;
*Not to be expected; only applicable when the site investigator is able to explicitly show a relationship*
Results in persistent or significant disability or incapacity;
*Not to be expected; only applicable when the site investigator is able to explicitly show a relationship*
Is a congenital anomaly or birth defect; (*Not applicable*) orAny other important medical event that did not result in any of the outcomes listed above due to medical or surgical intervention but could have been based on appropriate judgement by the investigator.

### Statistical analysis

### Primary and secondary study parameter(s)

Statistical analysis will be done according to intention-to-treat principle. All randomised participants will be included. The primary outcome is DCFDs, defined as the number of days in the first 14 days after randomisation during which the patient is alive without delirium and not in coma from any cause.^7^ Patients who are discharged before the 14-day study period has ended will be recorded as delirium and coma free after discharge.^8 35^ In addition, we will assume all patients who died within 14 days after randomisation to have 0 DCFDs.^7^ Differences between DCFDs between the haloperidol group and placebo group will be analysed using Poisson regression analysis, with adjustment for differences in baseline characteristics between treatment groups (when present) and for the different centres. We will collect data with regards to baseline demographics: age, sex, admission diagnosis category, APACHE II and APACHE IV, Sequential Organ Failure Assessment (SOFA) score, ICU days before study entry and pre-admission delirium duration in participants with delirium on admission. Pre-defined sub-analyses will include efficacy stratified by (1) agitated, mixed-type or hypoactive delirium; (2) the presence of hallucinations or delusions; (3) delirium severity (based on ICDSC score: low delirium severity=mean ICDSC score of 4 to 5; medium delirium severity=mean ICDSC score 5 to 7; high delirium severity=ICDSC score 7 to 8); and (4) sedation-related, hypoxic, metabolic or septic delirium. For cognitive and functional outcomes assessed with designated test batteries, non-parametric or parametric tests will be used depending on normality of scaled test results. Mortality risk will be assessed as a binary endpoint. A more detailed statistical analysis plan, to be drawn up before Data Base Lock, will be drafted for publication separately.

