### Sample size calculation

To achieve statistically significant results (p<0.05) with a power of 90% and a true treatment difference of 1 day for the primary outcome (from 3.2 DCFDs in the placebo group to 4.2 in the haloperidol group, SD in both groups is equal to 4.2), 371 patients are needed in each group (n=742). These estimates are derived from the previous implementation study, which included 4727 patients in three 4-month periods in the same six participating ICUs and found delirium incidence of 27% (and increase of DCFDs from 60% to 70%).^33^ Consequently, presuming an informed consent rate of 40%, we need 18 months to encounter 1900 patients with a newly diagnosed delirium to include the required 742 patients. Because of estimated workload due to follow-up visits, including, for example, neurocognitive testing, we propose to select a convenience sample of two-thirds of ICU survivors (estimated around 400 of 575 survivors) as a random sample for the cognitive, functional and secondary outcome variables.

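### Poisson regression is named for the primary outcome with no allowance for overdispersion, while the sample size assumes a variance 4.2 to 5.5 times the mean

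*Protocol article*

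**What the plan says.** The protocol article, under Statistical analysis, Primary and secondary study parameter(s), states: "Differences between DCFDs between the haloperidol group and placebo group will be analysed using Poisson regression analysis". The model is to adjust for centre and for any imbalance found at baseline. The abstract repeats the choice: "Differences in DCFDs between haloperidol and placebo group will be analysed using Poisson regression analysis". Neither place mentions a dispersion parameter, a robust variance or another count model. A more detailed analysis plan is announced for later and is not shown.

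The same section defines the outcome as a count bounded at 0 and 14, "defined as the number of days in the first 14 days after randomisation during which the patient is alive without delirium and not in coma", and adds two scoring rules:
- For deaths, "we will assume all patients who died within 14 days after randomisation to have 0 DCFDs".
- For early discharge, "Patients who are discharged before the 14-day study period has ended will be recorded as delirium and coma free after discharge".

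Sample size calculation gives the planning values: "from 3.2 DCFDs in the placebo group to 4.2 in the haloperidol group, SD in both groups is equal to 4.2". With 90% power and a 0.05 significance level it arrives at 371 patients per group, 742 in total.

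**The concern.** A Poisson model has one parameter for both mean and variance. At a mean of 3.2 it implies an SD of √3.2 = 1.79, but the trial was sized with 4.2. If the model's own standard errors are used, the primary confidence interval is too narrow and the p value too small, whatever the drug does.

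The scoring rules make this structural. Deaths are placed at 0, early discharge pushes patients towards 14, and nothing can exceed 14, so values gather at both ends. A Poisson distribution with mean 3.2 gives only e^(-3.2) = 4% zeros.

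The final test and possibly the interim looks are at stake. The article plans interim analyses at one-third and two-thirds of the trial, and its section on premature termination lists a significant benefit at interim among the reasons to stop. The same understated errors, if used there, would feed that decision.

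**Working it through.** **Inputs.** Means of 3.2 and 4.2, SD 4.2 in both arms, power 90%, alpha 0.05 and 371 per arm all come from Sample size calculation. Sidedness is not stated; the two-sided test reproduces the stated number.

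**1. Reproduce the plan's sample size.** For a two-sample comparison of means:

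n = 2 × (1.96 + 1.2816)² × 4.2² / 1² = 370.7, so 371 per arm and 742 in total. This matches exactly. The one-sided version gives 303 and does not match.

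**2. Sample size if the outcome were truly Poisson.** On the log scale:

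n = (1.96 + 1.2816)² × (1/3.2 + 1/4.2) / [ln(4.2/3.2)]², or about 79 per arm.

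The plan's 371 therefore already allows for a variance that the named model does not.

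**3. Effect on the standard error and the test.** Let φ = SD²/mean. The ratio of the model-based to the true standard error is 1/√φ. The actual two-sided error at nominal 5% is 2 × [1 − Φ(1.96/√φ)].

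| Common mean under the null | φ | SE ratio | Type I error, formula | Simulated, model-based | Simulated, robust |
|---|---|---|---|---|---|
| 3.2 | 5.51 | 0.43 | 40.4% | 40.3% | 5.4% |
| 3.7 (midpoint) | 4.77 | 0.46 | 36.9% | 36.7% | 5.0% |
| 4.2 | 4.20 | 0.49 | 33.9% | 33.6% | 4.8% |

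The simulations used 20,000 trials per row, 371 per arm, and a beta-binomial outcome on 0 to 14 with the stated mean and SD. The bounded scale therefore does not change the result.

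**4. Allowing for covariate adjustment (assumption).** Suppose centre and baseline covariates explain a share R² of the variance, so that φ becomes 17.64 × (1 − R²)/mean.
- R² = 10%, mean 3.2: φ = 4.96, SE ratio 0.45, type I error 37.9%.
- R² = 30%, mean 4.2: φ = 2.94, SE ratio 0.58, type I error 25.3%.

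Across R² of 10-30% the range is about 25-38%.

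**5. Allowing for a higher mean (assumption).** Sample size calculation also mentions a rise in DCFDs from 60% to 70%. If these are shares of 14 days, the means are 8.4 and 9.8. With the SD kept at 4.2:
- Mean 8.4: φ = 2.10, type I error 17.6% (simulated 17.4%).
- Mean 9.8: φ = 1.80, type I error 14.4% (simulated 14.4%).

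**6. Check of the remedy.** With a robust variance on the same log-link mean model, simulated type I error was 4.8-5.4% across all five means. Simulated power at 3.2 versus 4.2 with 371 per arm was 90.0%. The log-scale formula with SD 4.2 asks for 387 per arm, slightly more than 371, so planned power is kept to within about a percentage point.

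**The case against.** The strongest reply is that the article does not say which standard errors will be used. A log-link Poisson mean model with a robust or scaled variance is still Poisson regression, and the remedy here is of that kind. The choice of variance estimator is often left to the analysis plan, which the article says will follow.

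That reply stands to this extent: a reader might infer that the plan commits to model-based errors, so that the primary p value is already invalid with a false-positive rate of 34-40%. The document does not support that. It names a model and leaves the variance open.

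The reply does not remove the point. This is more than silence on a detail, because the standard variance of the model the article names conflicts with the SD the same article uses to size the trial.

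A second reply is that the rate depends on the planning figures. They come from an earlier implementation study, and the article does not say whether that study counted days after discharge in the same way. Covariate adjustment also reduces the inflation. Both are fair, so 34-40% is the unadjusted rate on the plan's own means and SD and not a bound. Neither alternative worked through above brings the rate near 5%.

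A reader might also infer that the sample size is wrong. It is not: 371 per arm reproduces exactly.

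**Conclusion.** The point holds in conditional form. The named primary model and the sample size rest on variances that differ by a factor of 4.2 to 5.5. If the model is run with standard model-based errors, the false-positive rate is several times the nominal level: about 34-40% unadjusted on the plan's figures, and about 25-38% or 14-18% under the two labelled assumptions. The direction does not depend on those assumptions; the size does. Because the primary test and interval depend on it, the variance estimator should be fixed in writing before any comparative analysis, including an interim one.

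**What to change.** Keep the log-link mean model with centre adjustment. State in the protocol and the analysis plan that the primary test and confidence interval, and any interim test of the primary outcome, use a robust (sandwich) variance, or a bootstrap or permutation test, and that model-based Poisson errors will not be used.

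The cost is one sentence and one software option. Outcome, mean model and sample size stay as they are. On the planning figures the reported unadjusted standard error becomes about 2.0 to 2.3 times the model-based one (1/0.488 to 1/0.426), so the interval is wider, but it matches the variance the trial was sized for.

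Two additions are optional and not needed to cure the fault: reporting the difference in mean DCFDs in days, the unit used for sizing, and a proportional-odds sensitivity analysis for the values gathered at 0 and 14.

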### Randomisation, blinding and treatment allocation

Legal representatives of eligible patients (when the patient is sedated or otherwise temporarily unable to consent) or the patient himself/herself will be asked for informed consent shortly after admission when the patient has no delirium or as soon as possible after admission when the patient already has delirium. Online supplemental appendix 6 contains an example of the patient consent form. In this study, the presence of delirium will be considered to be confirmed when the bedside nurse deemed the patient to have delirium based on assessment with the ICDSC or CAM-ICU, given the previous large-scale implementation project.^33^

10.1136/bmjopen-2019-036735.supp6Supplementary data

Delirious patients who fulfil all inclusion but no exclusion criteria, and for whom written informed consent has been obtained (as recorded in medical file), will be randomised. Randomisation coordination and start of a new case record form (CRF) will be guided by the electronic data capture (EDC) system of ALEA, constructed by the Clinical Trial Centre of the Erasmus Medical Centre and calibrated with the coordinating (Erasmus MC) and local pharmacies. We will randomise the recruited patients using a block design of eight patients in one block, and one block is assigned to a centre. We will have eight batches (numbered 1 through 8) of treatment and placebo, with four batches of placebo and four treatment (haloperidol). Each block will have a random assignment of eight batch numbers, having four placebo and four haloperidol patients included (a combination of 1 to 4 and 5 to 8 in random order). After eight patients are included in the study (ie, a block is full), a new block will be assigned to a centre.

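### Apart from centre, baseline covariates enter the primary model only if the arms differ, so the covariate set follows chance imbalance and not prognosis

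*Protocol article*

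**What the plan says.** The protocol article, under Primary and secondary study parameter(s), sets the primary analysis as a Poisson regression of DCFDs "with adjustment for differences in baseline characteristics between treatment groups (when present) and for the different centres". Centre is unconditional; every other baseline variable is conditional on a difference between the arms. The text does not say what counts as a difference, how it is assessed or who decides.

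The next sentence lists the baseline data: "We will collect data with regards to baseline demographics: age, sex, admission diagnosis category, APACHE II and APACHE IV, Sequential Organ Failure Assessment (SOFA) score", followed by time in the ICU before entry and, for patients already delirious on admission, how long the delirium had lasted before admission. That makes eight variables. None is committed to the model.

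Under Randomisation, blinding and treatment allocation, study centre is the only stratification factor.

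For the cognitive and functional scores, the same analysis section states that "non-parametric or parametric tests will be used depending on normality of scaled test results". A more detailed SAP is promised before database lock; it is not shown.

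**The concern.** With randomisation stratified only by centre, any difference between the arms in age, severity or diagnosis is chance. Chance imbalance is a poor reason to put a covariate in the model; the useful question is whether the variable predicts DCFDs. Deaths within 14 days are scored as 0 DCFDs, so variables that predict early death are plausible predictors of the outcome. The rule leaves them out whenever they happen to balance.

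Two things are at stake. First, the primary model cannot be written down until the arms have been compared. Without a criterion, its content ranges widely: read literally, almost any continuous variable differs slightly, so everything enters; read strictly, perhaps nothing does. That leaves room to choose a model after the data are seen. Second, precision available from variables the trial already collects is given up.

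The rule for the cognitive and functional scores is a different kind of dependence. It looks at the distribution of the outcome, not at balance between arms, and it concerns secondary outcomes.

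**Working it through.** **Inputs from the protocol article.** Sample size calculation: p<0.05, 90% power, a difference of 1 day ("from 3.2 DCFDs in the placebo group to 4.2 in the haloperidol group, SD in both groups is equal to 4.2"), 371 per group and 742 in total. Randomisation: equal allocation ("Each block will have a random assignment of eight batch numbers, having four placebo and four haloperidol patients included"). Statistical analysis: eight baseline variables.

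**Assumptions, not in the documents.** The covariates explain a share R² of DCFD variance beyond centre (10–20%, with 5–30% shown as a range). A difference means p<0.05 in a baseline comparison. The baseline variables are independent. A linear model stands in for the Poisson model.

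**1. The plan's own figure.** n per group = 2 × (1.960 + 1.282)² × 4.2² / 1² = 2 × 10.507 × 17.64 = 370.7, so 371, or 742 in total. This reproduces the stated number. Power at 371 per group: 1 / (4.2 × √(2/371)) = 3.243, and Φ(3.243 − 1.960) = 0.900. Sidedness is not stated; a one-sided test would need only 303, so the plan's figure is two-sided. It contains no covariate gain.

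**2. How often the rule would bring in a covariate by chance.** With eight independent variables, 1 − 0.95⁸ = 0.337. This is an upper figure: the two APACHE scores and SOFA are likely correlated, and pre-admission delirium duration exists only for a subset. Counting the three severity scores as one and dropping that duration leaves five variables: 1 − 0.95⁵ = 0.226. Either figure is the frequency with which the model changes, not an error rate.

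**3. Power with a fixed covariate set.** Power = Φ(3.243 / √(1 − R²) − 1.960).

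| Assumed R² | Power at 371 per group | n per group for 90% power |
|---|---|---|
| 0.05 | 0.914 | 353 |
| 0.10 | 0.928 | 334 |
| 0.20 | 0.952 | 297 |
| 0.30 | 0.972 | 260 |

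**4. What the conditional rule delivers.** Simulation of 742 patients, eight independent normal covariates of which three are prognostic, a linear model, and 10,000 runs per scenario. Conditional means adjusting only for covariates imbalanced at p<0.05; fixed means always adjusting for the three prognostic ones.

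| R² | Power: none / conditional / fixed | Type I error: none / conditional / fixed | Type I error if the most favourable of the three is picked |
|---|---|---|---|
| 0.10 | 89.7 / 90.1 / 92.5% | 4.9 / 4.5 / 4.6% | 6.3% |
| 0.20 | 90.2 / 90.9 / 95.2% | 4.7 / 4.3 / 4.8% | 7.1% |
| 0.30 | 90.0 / 91.3 / 97.2% | 5.0 / 4.4 / 5.3% | 7.8% |

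Share of the power gain kept by the conditional rule: at R² 0.10, (0.9005 − 0.8974) / (0.9253 − 0.8974) = 0.0031 / 0.0279, about 11%. At R² 0.20, (0.9094 − 0.9016) / (0.9515 − 0.9016) = 0.0078 / 0.0499, about 16%. Most of the gain is lost.

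**The case against.** **The SAP will settle it.** The covariate list and the test for each score normally belong in the SAP, and one is promised before database lock. Their absence here is indeed no fault. What stands is that the protocol states a principle, with imbalance as the trigger. An SAP that follows it inherits the problem; one that fixes covariates for prognosis has to depart from it.

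**Validity is not at risk.** A reader might infer that data-dependent adjustment inflates type I error. Applied mechanically it does not: the trigger looks at baseline data, not outcomes, and the simulated rate was 4.3–4.5%. The 6.3–7.8% arises only if someone picks the most favourable of three models. The document does not suggest that anyone would, and an SAP fixed in time would prevent it. It shows the room that a missing criterion leaves, not a forecast.

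**The trial keeps its planned power.** A reader might also infer that the trial is underpowered. It is not on this account: 742 patients give 90% power under the plan's assumptions with no adjustment. What is forgone is additional precision.

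**The size is soft.** This stands. No passage shows that any listed variable predicts DCFDs, the p<0.05 trigger is assumed, and the formula is for means. The outcome is bounded at 14 with deaths at 0, and the planning variance (4.2² = 17.64) far exceeds the mean (3.2), so the linear figures do not carry over directly to the Poisson model.

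**Centre is already handled.** It is, and nothing there needs to change.

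**Conclusion.** The concern holds for baseline characteristics other than centre. The stated rule makes the primary model depend on chance imbalance, without a criterion, and omits prognostic variables that happen to balance. The consequences are lost precision and room to choose the model after the arms are compared. The documents do not support a claim of inflated type I error under mechanical use, or of lost planned power.

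The illustrative size is a rise from 90% to about 93–95% power with fixed adjustment, most of it lost under the conditional rule. This rests on an assumed R² of 10–20% beyond centre, independent covariates, a p<0.05 trigger for the conditional rule and a linear approximation. The direction is secure; the amount is not.

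The normality-driven choice for cognitive and functional scores is a separate and less serious point, with no magnitude attached.

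**What to change.** Delete the condition that a difference must be present. Before any comparison of the arms, fix a short covariate list chosen for expected prognosis from variables already collected for all patients, and keep centre in the model. A workable example is age, one of the two APACHE scores, baseline SOFA, admission diagnosis category and ICU days before entry. State the time point of the SOFA score, which the article does not give. Leave out pre-admission delirium duration, because it is collected only in patients who were delirious on admission.

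For each cognitive and functional score, name one analysis method in advance, whatever the distribution turns out to be. Regression with robust standard errors is one acceptable choice among several.

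The cost is two sentences, in the protocol or in the promised SAP. It needs no new data and no change to the sample size.
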